## Objectives

### Primary objective

#### Phase 1-Needs assessment.

To assess functional decline and determine prevalent health conditions and risk factors among middle-aged and elderly tribals, in selected blocks of East Singhbhum district.To evaluate the quality of life and associated health determinants, including prevalent risk factors, among the same population groups in the study area.

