### Sample size

#### Quantitative component.

The sample size was determined using Cochran’s formula for large populations, utilizing the reported 34.3% prevalence of functional disability among rural older adults from the Longitudinal Ageing Study in India (LASI) Wave 1 as the reference estimate [5].

This reference proportion (p) was applied alongside a 95% confidence level and a 5% margin of error to calculate an initial requirement of 346 participants. To account for the multistage cluster sampling design, a design effect of 1.5 was applied, resulting in a final target sample size of 520. The formula used here is as follows:

$$\begin{array}{c} n\;=\frac{\left(z^{\text{2}}*\;\hat{p}\left(\text{1}\;-\;\hat{p}\right)\right)}{\varepsilon^{\text{2}}}\;(\text{4}) \end{array}$$

where:

n = required sample sizeZ = 1.96 (95% confidence level)p = 0.343 (estimated prevalence of functional disability)1 − p = 0.657d = 0.05 (absolute precision)

Substituting these values:

n=(0.05)2(1.96)2×0.343×0.657=346

As the study will employ a multistage cluster sampling approach, a design effect (DEFF) of 1.5 was applied to account for clustering of observations. This yielded a final sample size of:

346 × 1.5 = 519

which was rounded to **520 participants.**

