### Expected outcome

#### Primary outcome.

Functional Decline: Assessment of loss of capacity to perform basic and instrumental activities of daily living among middle-aged and elderly tribal individuals.Quality of Life (QoL): Assessment of physical, psychological, social, and environmental well-being.Health and Morbidity Profile: Assessment of prevalent chronic conditions, such as hypertension and diabetes, and associated risk factors at baseline.Model Effectiveness: Assessment of short-term changes in mobility, ADL performance, self-rated health, and QoL following pilot implementation.

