### Outcome measures and assessment timeline

#### Detailed data analysis.

A comprehensive statistical analysis plan for this study employs a multi-layered approach to address both quantitative and qualitative data strands, ensuring that the results are robust and account for the complexities of a tribal setting.

Quantitative Analysis Plan

Quantitative data will be processed and analysed using Jamovi statistical software.Descriptive Statistics: Continuous variables, including age, ADL/IADL scores, and WHOQOL-BREF scores, will be summarised using means, medians, and standard deviations.Categorical variables, including gender, tribal group, and chronic disease status, will be presented as frequencies and percentages.Bivariate Analysis: Chi-square tests will be used to assess associations between categorical variables, such as gender and functional decline.Comparison of Groups: Independent t-tests or ANOVA will be used to compare mean functional and quality-of-life scores across relevant groups, such as age categories and nutritional status.Correlation Analysis: Pearson’s or Spearman’s correlation coefficients will be used to examine relationships between functional status (ADL/IADL) and quality-of-life measures.

2. Qualitative Analysis Plan

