Quantitative findings: Establish the prevalence and measurable patterns of functional decline, quality of life, and related health conditions.Qualitative findings: Provide contextual insights into the cultural, social, and healthcare-related factors underlying these findings.Integrated interpretation: The combined findings will directly inform the three-step healthcare model development process, beginning with domain identification and confirmation based on both quantitative evidence and qualitative themes.

4. Managing Confounding Factors

To minimize potential confounding, multivariable logistic regression models will be used to assess the independent associations with functional decline and quality of life.Adjustment for Confounders: Models will adjust for potential confounders, including age, gender, nutritional status, and the presence of chronic conditions.Stratification: Where appropriate, analyses will be stratified by gender to examine differences in health needs, occupational risks, and intervention-related outcomes between men and women.

5. Handling Missing Data

Prevention of Missing Data: Community sensitisation and support from Sahiya/ASHA workers will be used to strengthen community participation and minimise non-response.Management of Missing Values: The extent and pattern of missing data will be assessed. Where appropriate, suitable statistical methods, such as multiple imputation, may be considered during the final analysis to minimise potential bias.Data Cleaning and Anonymisation: Data will be systematically checked and cleaned before analysis. Unique identification codes will be used to maintain participant confidentiality and facilitate data management.

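### WHOQOL-BREF scores are handled as continuous in the descriptive and unadjusted analyses, but the only adjusted model named for quality of life is logistic regression

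*Protocol article*

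**What the plan says.** Quality of life belongs to the primary objective of Phase 1: "To evaluate the quality of life and associated health determinants, including prevalent risk factors, among the same population groups in the study area". It is also listed under Expected outcome, Primary outcome: "Quality of Life (QoL): Assessment of physical, psychological, social, and environmental well-being".

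The quantitative part of Detailed data analysis keeps the score on its numerical scale three times:

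- Description: "Continuous variables, including age, ADL/IADL scores, and WHOQOL-BREF scores, will be summarised using means, medians, and standard deviations".
- Group comparison: "Independent t-tests or ANOVA will be used to compare mean functional and quality-of-life scores across relevant groups".
- Correlation: "Pearson’s or Spearman’s correlation coefficients will be used to examine relationships between functional status (ADL/IADL) and quality-of-life measures".

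Item 4 of the same section (Managing Confounding Factors) then turns to adjusted analysis: "multivariable logistic regression models will be used to assess the independent associations with functional decline and quality of life". The covariates follow: "Models will adjust for potential confounders, including age, gender, nutritional status, and the presence of chronic conditions". The article names no linear or other continuous-outcome model, and it gives no category or threshold for quality of life.

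**The concern.** One outcome is continuous when unadjusted and, on the usual meaning of logistic regression, binary when adjusted. This is more than a missing detail, because the article fixes the model type and that type does not suit the outcome as described a few lines earlier.

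The adjusted model is the only analysis that can say which determinants of quality of life stand after allowing for the others, which is what the second part of the primary objective needs. Its results also feed the choice and ranking of domains for the Phase 2 model. Splitting the score costs precision for every determinant. It also leaves the adjusted results as odds ratios, which cannot be set directly beside the unadjusted mean differences.

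**Working it through.** **The plan's own figure.** The sample size section uses z = 1.96, p = 0.343 and d = 0.05:

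n = 1.96² × 0.343 × 0.657 / 0.05² = 346.3, taken as 346; 346 × 1.5 = 519, rounded to 520.

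This reproduces. It rests on functional disability ("utilizing the reported 34.3% prevalence of functional disability among rural older adults") and uses no quality-of-life input, so nothing below changes it.

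**Inputs for the check.** N = 520 and the design effect of 1.5 come from the article. It gives no cut, standard deviation, effect size or distribution for WHOQOL-BREF, so these are assumptions: normal residuals first, then other shapes, with cuts from the 10th to the 50th percentile. Applying 1.5 to quality of life is also an assumption, since the article sets it for a prevalence.

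**Formula.** For a normal score cut so that a share q lies below, the efficiency of the binary analysis relative to the linear one, for small effects, is

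RE = φ(z_q)² / [q(1 − q)].

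- Median: 0.3989² / 0.25 = 0.637, which is 2/π. The standard error rises by √(π/2) = 1.253, about 25%.
- 25% cut: 0.318² / 0.1875 = 0.539.
- 20% cut: 0.280² / 0.16 = 0.490.

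| Share below cut | RE | Loss | 520 act like | 520/1.5 = 346.7 act like |
|---|---|---|---|---|
| 50% | 0.637 | 36.3% | 331 | 221 |
| 34.3% | 0.600 | 40.0% | 312 | 208 |
| 25% | 0.539 | 46.1% | 280 | 187 |
| 20% | 0.490 | 51.0% | 255 | 170 |
| 10% | 0.342 | 65.8% | 178 | 119 |

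**Power.** With 260 against 260 and two-sided α = 0.05, a standardised difference of 0.246 has 80% power on the continuous score and about 61% after a median split. At a difference of 0.25 the figures are 81% and 62%, or 64% and 46% with the design effect of 1.5.

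**Simulation.** In 1,000 data sets of 520 with normal residuals, a true group difference of 0.25 SD and one covariate, the squared ratio of mean z (logistic to linear) was 0.63 for a median split and 0.59 for a cut at 34.3%. Power was 79.5% for linear regression against 61.5% and 58.9%. This agrees with the formula.

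**Other residual shapes.** The general form is RE = σ² f(c)² / [q(1 − q)].

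| Residual shape | Loss at median | Loss at 25% cut |
|---|---|---|
| t, 5 df | 4% | 30% |
| logistic | 18% | 38% |
| t, 10 df | 24% | 40% |
| normal | 36% | 46% |
| beta(5,3) | 46% | 58% |
| uniform | 67% | 56% |

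With Laplace residuals the order reverses at the median (the split beats least squares), and the loss at the 25% cut is 33%. Heavy tails are less plausible than bounded shapes for a bounded score, but the article does not settle the question.

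**The case against.** Several points count on the other side.

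- **A category may be intended.** Item 3 of the analysis section speaks of establishing prevalence and patterns for quality of life along with functional decline. Prevalence implies a class, and modelling who has poor quality of life is a defensible aim in a needs assessment. This stands as a reason to allow a binary model as an addition. It does not explain why the only adjusted model should drop the scale used in the other analyses.
- **Logistic need not mean binary.** An ordinal logistic model needs no single cut. In 100 simulated data sets with ten categories it kept about 94% of the information. The text does not say ordinal, and the plain term normally means binary, but it would be wrong to say that the plan forces a split.
- **The cut may be defined elsewhere.** A reader might infer that the threshold would be chosen after seeing the data. The article does not say so, and an analysis plan not shown could hold it. The missing threshold is therefore not the finding.
- **Functional decline has the same pattern.** ADL and IADL scores are also listed as continuous and also go into the logistic model. There, however, the study was sized on a prevalence, so a binary outcome matches the design. Quality of life has no such anchor.
- **Scales can be reconciled.** Crude odds ratios could be reported beside adjusted ones, so the mismatch with the mean differences is an inconvenience rather than an error.

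**Conclusion.** The point holds as a mismatch between the stated model and the stated scale of a primary outcome. On the ordinary reading of the text, and if residuals are roughly normal, the adjusted quality-of-life models lose about 36% of the information with a median split and 46% to 51% with a 25% or 20% cut.

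A reader might infer that at least a third is always lost. The documents do not support that as a floor, because they give no distribution and heavier tails bring the loss below it. Nor do they support the inference that the study is undersized: the 520 rests on precision for functional disability, and no quality-of-life power claim is made. The descriptive, t-test, ANOVA and correlation analyses keep the score continuous and are unaffected. The study remains valid, but its adjusted answer on quality of life would be less precise than the same data allow.

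**What to change.** In item 4 of Detailed data analysis, state that each WHOQOL-BREF domain score will be analysed on its continuous scale by multivariable linear regression with the covariates already listed, reporting adjusted mean differences with 95% confidence intervals. Keep logistic regression for the binary functional-decline outcome. If a poor-quality-of-life category is also wanted for prevalence, prespecify its cut and report that model as secondary.

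This takes a sentence or two and no new data. The price is that adjusted quality-of-life results are expressed as mean differences rather than odds ratios. The timeline has data collection ending on 15 September 2026 and analysis on 15 November 2026, so the change should be settled before analysis begins. How the models allow for village clustering is a separate question, and this change does not depend on it.

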#### Step 2: Stakeholder Consultation and Healthcare Model Development.

A draft model will be developed using evidence-based, culturally appropriate strategies. It will be refined through stakeholder consultations (tribal leaders, ASHAs, NGOs, public health experts, Pradhan etc.) to ensure feasibility and acceptability, leading to finalisation of domains and model. A gender-stratified approach will guide tailored interventions. The healthcare model will adopt a gender-stratified approach, using questionnaire findings to identify gender-specific health needs, risks, and barriers and design tailored interventions. For men, this will focus on non-communicable diseases, substance abuse, and occupational risks, while for women, it will address reproductive health, nutrition, chronic conditions, and caregiver burden. Service delivery will also be adapted, with community or workplace outreach for men and mobile camps, home visits, and empowerment initiatives for women, ensuring a holistic response to biological, social, and cultural determinants of health.

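### Stratifying by gender gives no estimate of a gender difference in a risk-factor association or in pre-post change; a gender interaction term with its interval would.

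*Protocol article*

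**What the plan says.** In the protocol article, Detailed data analysis, item 4 (Managing Confounding Factors) states that, where appropriate, "analyses will be stratified by gender to examine differences in health needs, occupational risks, and intervention-related outcomes between men and women". The sentence names both a method, stratification, and its purpose, examining male-female differences.

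Gender appears in two other places in the quantitative plan:

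- As an adjustment variable in the regression. The article says that "multivariable logistic regression models will be used to assess the independent associations with functional decline and quality of life", and "Models will adjust for potential confounders, including age, gender, nutritional status, and the presence of chronic conditions".
- As an example in the bivariate analysis: "Chi-square tests will be used to assess associations between categorical variables, such as gender and functional decline". The same section plans t-tests or ANOVA across relevant groups.

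The article names no interaction term and no other formal comparison of the male and female results.

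The gender findings have a use downstream. Under Step 2 of Phase 2, the care model takes a gender-stratified approach, "using questionnaire findings to identify gender-specific health needs, risks, and barriers and design tailored interventions".

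**The concern.** The sentence on stratification covers three targets, and they need different statistics.

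- **Health needs** are mostly differences in level, for example whether functional decline is more common in women. A direct comparison of the two groups answers this, and one is planned.
- **Occupational risks** include the question whether a factor's association with functional decline is stronger in one gender. This is a difference between two associations.
- **Intervention-related outcomes** include the question whether the pre-post change in the pilot village differs by gender. This is a difference between two changes.

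For the last two, separate strata give two estimates and nothing that measures the gap between them. The other planned uses of gender do not fill this gap. The chi-square test concerns the outcome level. Gender as a main-effect covariate assumes that the other factors act equally in men and women.

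A reader left with two separate tables may compare them by which results reach significance. That comparison is unreliable: two strata with the same true effect and moderate power often fall on opposite sides of the 5% threshold. False gender-specific risks could then enter the discussion of what to offer men and women, and real differences could be missed.

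**Working it through.** **Reproducing the plan's figure.** Inputs from the Sample size section: "p = 0.343 (estimated prevalence of functional disability"; "This reference proportion (p) was applied alongside a 95% confidence level and a 5% margin of error"; "a design effect of 1.5 was applied, resulting in a final target sample size of 520".

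n = 1.96² × 0.343 × 0.657 / 0.05² = 346.27, taken as 346. Then 346 × 1.5 = 519, rounded to 520. The stated figure reproduces.

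**Assumptions not in the article.** A 50:50 gender split (260 each), a binary factor held by half of each gender, the same true OR in men and women, and two-sided alpha of 0.05. Overall prevalence is the article's 0.343. The design effect is 1 (no clustering) or the article's 1.5.

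**Step 1: power within one gender.** Choose p0 and p1, the prevalence without and with the factor, so that their mean is 0.343 and their odds ratio is the assumed OR. With n per exposure group = 130, or 130/1.5 = 86.7:

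z = (p1 − p0) / √[p0(1 − p0)/n + p1(1 − p1)/n], and power P ≈ Φ(z − 1.96).

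At OR 2.0, p0 = 0.266 and p1 = 0.420.

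- Design effect 1: z = 0.154/0.0581 = 2.65, so P = 0.756.
- Design effect 1.5: z = 0.154/0.0712 = 2.17, so P = 0.582.

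**Step 2: chance that exactly one gender is significant although the effects are equal.** This is 2P(1 − P). At OR 2.0 it is 2 × 0.756 × 0.244 = 0.369, and 2 × 0.582 × 0.418 = 0.487.

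| True OR, both genders | Design effect 1 | Design effect 1.5 |
|---|---|---|
| 1.25 | 24% | 19% |
| 1.5 | 45% | 37% |
| 1.75 | 49% | 49% |
| 2.0 | 37% | 49% |
| 2.5 | 11% | 30% |
| 3.0 | 2% | 13% |

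**Sensitivity.** A Wald test on the log odds ratio gives similar values: 38% and 49% at OR 2.0, and 14% and 33% at OR 2.5. With a 40:60 gender split or a factor held by 30%, the Wald values for OR 1.5 to 2.5 run from 17% to 51%. With no effect in either gender, about 9% of cases would show one significant stratum.

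**Step 3: the interaction test on the same data.** In simulation (40,000 runs per setting, equal ORs from 1 to 3), testing the difference between the two log ORs called them different in 4.6% to 5.1% of runs.

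**Step 4: what the interaction test can detect.** The standard error of the difference in log ORs is about √[4/(n × 0.343 × 0.657)].

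- n = 130: √(4/29.3) = 0.370. The ratio of ORs detectable with 80% power is exp(2.80 × 0.370) ≈ 2.8.
- n = 86.7: √(4/19.5) = 0.453. The ratio is exp(2.80 × 0.453) ≈ 3.6.

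**Step 5: pre-post change.** The number of pilot participants is not given. Assuming 10 to 40 per gender and an equal standardised change of 0.3 to 0.7, a paired t-test in each gender gives a chance of 2% to 50% that exactly one is significant.

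**The case against.** A reader might infer that the investigators will declare a gender difference whenever one stratum is significant and the other is not, and that equal effects will therefore often be reported as gender-specific. The article does not support that. It gives no decision rule, it limits stratification to where it is appropriate, and stratified tables are compatible with comparing estimates and intervals or with adding an interaction term. The percentages above are conditional on a reading that the plan neither states nor excludes.

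It can also be said that a condensed article may leave interaction terms to a fuller plan. This has some force. But the article does more than stay silent: it names a method for examining differences, and for two of the three targets that method alone does not yield the difference.

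Three further points stand and limit the finding:

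- Differences in level are already compared directly, so they need no interaction term.
- The risk depends on effect size. It is small at OR 3, and at OR 2.5 without clustering it is 11%.
- The care model does not rest on these analyses alone. Step 2 already names topics for men and for women and adds stakeholder consultation, and the section on model refinement sets gender patterns beside qualitative evidence.

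The remedy has limited power, since only large ratios of ORs would be detected reliably. That argues for reporting an interval rather than a verdict. It is not a reason to leave the difference unestimated.

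**Conclusion.** The point holds in a limited form. For gender differences in associations and in pre-post change, the stated method provides no estimate, interval or test of the difference. For differences in level there is no gap.

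If strata were compared by significance, the chance of an equal effect looking gender-specific would be far above the roughly 5% of an interaction test for moderate effects, and would approach or fall below it only for large ones. The size rests on the assumed gender split, factor prevalence and odds ratios, none of which the article gives. The pilot figure is rougher still, because the number of participants per gender is unknown.

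The consequence is moderate: these results are one input, with qualitative evidence and stakeholder consultation, to the gender-tailored model. The change is still worth making because a better method is available at almost no cost.

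**What to change.** In item 4 of Detailed data analysis, add: *Differences between men and women in associations (for a few named factors) and in pre-post change will be estimated with a gender interaction term and 95% confidence interval; gender-specific results are descriptive.* Name the factors in advance; nutritional status, chronic conditions and occupation are natural candidates from the article's own lists. Base any statement of a gender difference in an association or change on that term.

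The cost is one sentence and a few model terms, with no new data. The article's timeline puts Phase 1 analysis after data collection ends on 15 September 2026, so the sentence can be fixed before the results are known.

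The downside is wide intervals, with 80% power only for a ratio of ORs of about 2.8 to 3.6. Report the terms as estimates, and do not read a non-significant term as showing no difference.

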#### Sources of bias and mitigation strategies.

The study identifies potential sources of bias related to participant selection, communication, measurement, and data management. Measures will be taken to reduce these biases and improve the validity of the findings.

Selection Bias

Source: Selection bias may arise if the study participants do not adequately represent the diversity of tribal populations in the study area.Mitigation: A multistage stratified random sampling approach will be used to enhance representativeness across tribal populations, including Scheduled Tribes (STs) and Particularly Vulnerable Tribal Groups (PVTGs). Villages will be selected across five blocks to ensure adequate geographical coverage.

2. Duplication and Participation Bias

Source: Bias may occur among individuals already participating in similar health interventions or research studies.Mitigation: Individuals currently enrolled in similar health-related interventions or research studies will be excluded to minimize duplication and potential influence on study outcomes.

3. Information and Communication Bias

Source: Differences in literacy, language, and cultural context may affect participants’ understanding of study information and interview questions.Mitigation: Village-level sensitization meetings will be conducted with community leaders, Sahiya/ASHA workers, and residents. Information will be provided in an understandable and culturally appropriate manner. For illiterate participants, consent will be documented through a thumb impression in the presence of a witness. Support from Sahiya/ASHA workers will also be sought to facilitate communication and community engagement.

4. Recall and Measurement Bias

Source: Participant recall and reliance on self-reported information may result in inaccurate reporting of health conditions or functional status.Mitigation: The concurrent mixed-methods approach will enable triangulation of findings across quantitative and qualitative data. Standardized and validated instruments, including the Barthel Index, Lawton IADL Scale, and WHOQOL-BREF, will be used to improve the consistency of measurement.

5. Data Management and Researcher Bias

Source: Access to personal identifiers may potentially influence data handling or compromise participant confidentiality.Mitigation: Participant identifiers will be removed or replaced with unique identification codes during data processing and analysis. Data will be securely managed to maintain confidentiality and support objective analysis.

6. Gender Bias

Source: Gender norms and the predominantly female composition of grassroots healthcare workers may limit the engagement of some male tribal community members with health services.

Mitigation: Preferably include male grassroots healthcare workers and tribal volunteers alongside female workers to facilitate gender-sensitive community engagement and ensure equitable participation and non-discriminatory service delivery.

